### Part A-Treatment group

Patients will receive an initial assessment and EBI from the ASN. The EBI can best be described as a motivational approach to helping individuals change their drinking behaviour. The intervention builds upon methods utilised to deliver BIs. However, as the intervention is delivered for approximately 20 minutes on up to six occasions the term "brief" is somewhat anomalous. We will therefore refer to this mode of delivery as an "extended brief intervention" (EBI). The intervention will be delivered utilising the FRAMES approach [25], and will be protocol driven with regular clinical supervision and observation to maximise intervention integrity. Each intervention will be documented and timed. The most important element of this model is the exploration of patients' perceptions as to the link between their alcohol consumption and presentation. The FRAMES [45] approach consists of the following:

FEEDBACK about personal risk or impairment;

RESPONSIBILITY: emphasis on personal responsibility for change;

ADVICE to cut down or abstain if indicated because of severe dependence or harm;

MENU of alternative options for changing drinking pattern and, jointly with the patient, setting a target;

EMPHATIC INTERVIEWING: listening reflectively without cajoling or confronting; exploring with patients the reasons for change as they see their situation;

SELF EFFICACY: an interviewing style that enhances peoples' belief in their ability to change.

A maximum of six treatment sessions, lasting 20 minutes each, will take place within the 12 week treatment period (2 hours in total). Follow-up visits will be scheduled 12 weeks and 6 months following recruitment into the study, and will be performed in the outpatients department, at home or by telephone. The assessor will be blinded to treatment allocation.

### Control group

The control group will receive the same assessments as the intervention group but they will not receive the EBI. They will receive normal clinical care, which may or may not include referral to a specialist alcohol service. Follow up visits will be arranged 12 weeks and 6 months following recruitment into the study, either in outpatients, at home or by telephone by a nurse researcher blinded to treatment group.

### Patient experience

The qualitative researcher (QR) conducting face-to-face interviews will receive contact information for patients consenting to this part of the trial. The QR will contact the patient to arrange a time and place for the interview. The patient experience part of the trial adopts a qualitative design and will focus on gaining the patient's views on three main features of the study: a) of being screened for alcohol-related problems, b) of being invited to take part in a treatment programme, c) of being randomized. It is designed to capture the patient's experience and more particularly the opportunistic nature by which they will have their drinking assessed and of their participation in the RCT. In-depth face to face interviews will be used to collect data using a topic guide. The topic guide is designed to elicit information about the following:

▪ The experience of the opportunistic nature of the screening.

▪ The experience of being offered and receiving a BI.

▪ The experience of being identified as alcohol dependent without being included in the intervention arm of the study.

The identification of themes and patterns in the interview data, using such techniques as constant comparative and deviant case analysis, will be the predominant method of organising, coding and categorizing the data.

### Economic Evaluation

For the economic analysis, Euroqol EQ 5D [46] will be utilised. EQ-5D is a standardised instrument for use as a measure of health outcome. The first part of the EQ-5D has 3-levels consisting of 5-dimensions including mobility, self care, usual activities, pain/discomfort, and anxiety/depression. The second part is a visual analogue scale (VAS) used by the patient to subjectively measure on a point interval scale their health status. Worst imaginable health state is scored as 0 at the bottom of the scale, and best imaginable health state is scored as 100 at the top.

The major part of the economic analysis will be a simple comparison of costs in the two arms, measuring the costs of providing the services against any differences in NHS costs between the two arms which might occur as a result of decreased use of all other services (for example, hospital reattendances, accidents, GP visits etc) regardless of their relationship to the abuse of alcohol. The perspective will be limited to that of the NHS. The time frame will be over the six months follow-up time of the study. The costs of the intervention will be as identified in the study. The costs of the use of NHS services (A/E or GP attendances, cost per bed day as an inpatient) will be taken from standard NHS costs published by the [47]. The total costs of NHS care for each patient will be based on these costs and on the amount of service utilisation data collected as outlined above. It may be necessary to adjust the analysis if there are differences in baseline SADQ or in comorbidities.

A separate analysis of NHS costs specifically for alcohol related services will need to be undertaken as a reduction in NHS service use may only be seen in alcohol-related areas, especially in patients with severe comorbidities. Whether a particular NHS intervention is related to alcohol or to another cause will require judgment, which will be undertaken by two clinical assessors who are blind to patient allocation.

If the costs (especially total costs but also alcohol only related costs, provided that non alcohol related costs are equal) in the intervention arm are less than in the non-intervention arm, then the economic case for the intervention is made. If the costs in the intervention arm are greater than in the non-intervention arm, it is necessary to undertake a cost effectiveness study, with the same time frame and perspective.

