### Secondary outcome measures

The secondary outcome measures are:

1. A change in AUDIT score from baseline at 12 weeks and at 6 months post randomisation. Although AUDIT is a screening test for alcohol use disorders [41], in common with other studies, we will in this context use it as both an outcome measure and a pre-screen to establish presence of alcohol dependence. The sum of the items scored has been used in several studies to indicate dependence and therefore will allow for comparability with other trial baseline and outcome measures [10].

2. Measure of alcohol dependence utilising the Leeds Dependency Questionnaire (LDQ) [42] at baseline, 12 weeks and 6 months post randomisation. The LDQ is a 10-item questionnaire designed to measure dependence upon a variety of substances including alcohol. The questionnaire includes 1 item from 10 markers that define dependence; these include pre-occupation, salience of alcohol, compulsion to start, planning around alcohol consumption, maximize effect, narrowing of use of repertoire, compulsion to continue, primacy of effect, constant state and cognitive set. Each item is scored 0-1-2-3, giving a maximum of 30 with higher score indicating greater degree of dependence.

3. Quantity and frequency of alcohol consumption in UK units per drinking day at baseline, 12 weeks and 6 months post randomisation.

4. Readiness to Change Questionnaire (RCQ) at baseline, 12 weeks and 6 months post randomisation. This is an important measure for non-treatment seeking populations as it has been demonstrated that treatment-seeking is an indication of treatment readiness, which has been seen as important in achieving treatment outcomes [20]. Using this measure will help us to investigate if treatment readiness does indeed have any bearing on treatment outcome in the population and setting.

5. Number of ED attendances 6 months pre and 6 months post treatment/control.

6. Hospital length of stay sum days in hospital 6 months pre and 6 months post randomisation.

7. Number of hospital admissions 6 months pre and 6 months post randomisation.

8. Length of stay for initial treatment in days.

9. Biochemical indicators of co-morbid conditions including Gamma-glutamyl transferase (GGT), Alanine aminotransferase (ALT) and mean corpuscular volume (MCV), when available will be extracted from a recent laboratory records; this is defined as the last available value prior to randomization.

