### Analysis of Health Economic measures

The economic analysis is designed to determine cost effectiveness for delivery of the clinical intervention protocol. This will include analysis of post intervention healthcare utilisation, and standard measures of changes in health status.

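### Adjustment of the cost comparison depends on the baseline imbalance observed, and hospital use before randomisation, although collected, is not named as a covariate

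*Protocol article*

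**What the plan says.** The Economic Evaluation section of the protocol article fixes the main analysis: "The major part of the economic analysis will be a simple comparison of costs in the two arms". On covariates it says only: "It may be necessary to adjust the analysis if there are differences in baseline SADQ or in comorbidities". It does not say how large a difference would trigger adjustment, which model would be used, or how comorbidity would be measured.

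The costs belong to the period after randomisation: "The time frame will be over the six months follow-up time of the study". The section Analysis of Health Economic measures agrees: "This will include analysis of post intervention healthcare utilisation, and standard measures of changes in health status".

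Under Secondary outcome measures, the same article collects hospital use on both sides of randomisation: "Number of ED attendances 6 months pre and 6 months post treatment/control" (item 5), "Hospital length of stay sum days in hospital 6 months pre and 6 months post randomisation" (item 6) and "Number of hospital admissions 6 months pre and 6 months post randomisation" (item 7). Neither economic section names these earlier counts as covariates.

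For the clinical scores the approach differs. The sections on the primary and secondary outcomes commit in advance to ANCOVA with the baseline value as covariate for SADQ, AUDIT, LDQ and RCQ, whatever the baseline table shows.

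**The concern.** A sentence that permits adjustment once a difference has been seen leaves two candidate estimates of the cost difference and no rule for choosing between them. The two variables it names may also not be the best available. A patient's own recent hospital use is the most direct baseline counterpart of later hospital cost, and it is already being extracted.

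The choice matters because the Economic Evaluation section attaches a decision to the result. Lower cost in the intervention arm is taken to settle the economic case; higher cost leads to a cost-effectiveness study. If the two estimates fall on opposite sides of zero, the choice between them changes what is concluded and what is done next.

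**Working it through.** The article states no cost standard deviation, correlation or power for costs, so there is no figure of its own to reproduce. The check has four steps.

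**1. Text.** The main analysis is unadjusted. Adjustment is conditional and tentative. Prior use is collected for ED attendances, bed days and admissions. The section Data collection/management process mentions GP and ambulance data but gives them no window before randomisation. A covariate built from prior hospital use is therefore supported; one built from total prior NHS cost is not.

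**2. Precision available from planned adjustment.** With a linear model and correlation r between the covariate and six-month cost, residual variance is multiplied by 1 − r², and the equivalent sample size by 1/(1 − r²). The values of r are assumptions.

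- r = 0.3: 1 − 0.09 = 0.91, a 9% reduction; 1/0.91 = 1.10
- r = 0.5: 1 − 0.25 = 0.75, a 25% reduction; 1/0.75 = 1.33
- r = 0.6: 1 − 0.36 = 0.64, a 36% reduction; 1/0.64 = 1.56

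**3. What adjusting only on imbalance delivers.** Simulation: 20,000 trials per row, 65 patients per arm (the evaluable number in the first sample size calculation), normal outcome with SD 1, no true difference, and one baseline covariate. Conditional means adjusting only when that covariate differs between arms at p < 0.05. The trigger is an assumption, because the article gives none.

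| r | SD of estimate: unadjusted | conditional | always adjusted | Type I error: unadjusted | conditional | always adjusted |
|---|---|---|---|---|---|---|
| 0.3 | 0.1745 | 0.1730 | 0.1677 | 0.049 | 0.048 | 0.050 |
| 0.5 | 0.1754 | 0.1693 | 0.1524 | 0.052 | 0.046 | 0.052 |
| 0.7 | 0.1771 | 0.1647 | 0.1258 | 0.053 | 0.037 | 0.049 |

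As a check, theory gives an unadjusted SD of √(2/65) = 0.175, which agrees. The share of the possible reduction in SD that the conditional rule achieves is:

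- r = 0.3: 0.0015/0.0068 = 22%
- r = 0.5: 0.0061/0.0230 = 27%
- r = 0.7: 0.0124/0.0513 = 24%

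Conditional adjustment therefore forgoes about three quarters of the gain. Its type I error is at or below the nominal level.

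**4. How often the two estimates disagree in sign.** With no true difference and large samples, the correlation between the unadjusted and adjusted differences is √(1 − r²). The probability of opposite signs is then arccos(√(1 − r²))/π = arcsin(r)/π: 10% at r = 0.3, 17% at r = 0.5 and 20% at r = 0.6. This shows how often the choice could alter the direction of the result. It is not an error rate of the plan.

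**The case against.** The strongest reply is that the main analysis is fixed and valid. In a randomised trial the unadjusted difference in mean cost is unbiased, and the sentence on adjustment can be read as a tentative contingency. A condensed article may leave covariates, model form and interval method to a fuller document. The first part stands: nothing here makes the unadjusted comparison wrong. The second does not answer the point, because the article itself states that adjustment would follow from observed differences, and it is that stated approach which is questioned.

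A reader might infer that choosing after seeing the baseline data inflates type I error. The documents do not support this, and the simulation points the other way (0.037 to 0.048). The simulation has its own limits. It used one covariate as both trigger and adjuster, with normal data, whereas the article names SADQ and comorbidities as triggers and costs may well be skewed. It shows the behaviour of such rules in general and does not model this trial.

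It can also be said that the costing sentence ("The total costs of NHS care for each patient will be based on these costs and on the amount of service utilisation data collected as" set out earlier) may reach back to the counts before randomisation. That wording does not exclude them, but the six-month follow-up time frame and the reference to utilisation after the intervention point to later costs only.

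The Blinding section keeps the statistician unaware of allocation, which limits the scope for picking a favourable estimate. The protection may be incomplete, because total cost includes the cost of an intervention that only one arm receives.

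Finally, omitting a prognostic covariate costs efficiency and is not an error, and no correlation in the article anchors the size of the gain. Both points are accepted.

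**Conclusion.** The point holds as a near-free improvement to a stated approach. Adjustment of the cost comparison hangs on observed imbalance, and hospital use before randomisation is collected but not put to use. The harm is lost precision and an avoidable choice between two estimates, in an analysis that carries a decision. Bias and type I inflation are not shown.

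The size is illustrative. A reduction in residual variance of 9% to 36% rests entirely on an assumed correlation of 0.3 to 0.6 and on a linear model, and should not be presented as an expected gain.

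A reader might also infer that pre-specified adjustment would make the economic conclusion secure. It would not. The Economic Evaluation section reads the conclusion from the direction of the cost difference without regard to its uncertainty, and the sign of an adjusted difference would then decide in the same way. That is a separate issue. The primary SADQ analysis, where baseline adjustment is already fixed, is unaffected.

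**What to change.** Replace the sentence on possible adjustment with:

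> The difference in six-month total NHS cost will be estimated by regression on arm, adjusted for 6-month pre-randomisation hospital use or cost (ED attendances, admissions, bed days), baseline SADQ and a comorbidity measure named in advance, whatever imbalance is observed, with bootstrap 95% confidence intervals; the unadjusted difference will be reported alongside.

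The covariate should be limited to hospital use unless GP and ambulance data are confirmed for the same earlier window. Its window should be defined once, because item 5 of the secondary outcomes is anchored to treatment or control while items 6 and 7 are anchored to randomisation.

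The cost is a change of analysis wording and the naming of one comorbidity measure. The hospital counts are already planned, and information on comorbidity is already collected at the baseline assessment. No added visits or patients are needed.

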### Overall aim of the study

To test the clinical and cost effectiveness of extended BI for individuals with alcohol dependence in an acute hospital setting.

The study objectives are:

1. To determine whether BI reduces overall alcohol consumption.

2. To determine whether BI is effective in the treatment of alcohol dependence.

3. To determine whether BI reduces the length of stay in hospital

4. To determine how patients feel about being approached in an opportunistic manner for screening for alcohol-related problems and subsequently being asked to be part of a research trial.

5. To determine the cost effectiveness of BI for alcohol dependence

The study is a randomized controlled trial. The study has been approved by North West Research Ethics Committee ref: 09/H1005/61, and is fully compliant with the Helsinki declaration 2008.

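### The economic decision rule turns on the direction of the cost difference alone, with no condition on health or uncertainty, and conflicts with the unconditional cost-effectiveness objective

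*Protocol article*

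**What the plan says.** All quotes are from the protocol article.

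- **Objective 5** (Overall aim of the study) is unconditional: "To determine the cost effectiveness of BI for alcohol dependence". Analysis of Health Economic measures likewise gives cost-effectiveness as the purpose of the economic analysis and includes measures of change in health status. The Abstract also promises an assessment of cost-effectiveness.
- **Main analysis** (Economic Evaluation): "The major part of the economic analysis will be a simple comparison of costs in the two arms". The perspective is the NHS. "The time frame will be over the six months follow-up time of the study".
- **Rule, lower-cost branch:** if the costs "in the intervention arm are less than in the non-intervention arm, then the economic case for the intervention is made". The costs that count are described as "especially total costs but also alcohol only related costs, provided that non alcohol related costs are equal".
- **Rule, higher-cost branch:** "If the costs in the intervention arm are greater than in the non-intervention arm, it is necessary to undertake a cost effectiveness study".
- **Health measure:** "For the economic analysis, Euroqol EQ 5D [46] will be utilised". Neither branch of the rule refers to it.
- **Adjustment:** "It may be necessary to adjust the analysis if there are differences in baseline SADQ or in comorbidities".

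**The concern.** The article could have left the economic methods to a fuller document. Instead it states the conclusion to be drawn and the condition for drawing it. That condition has four weaknesses.

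1. **No health condition.** Lower cost supports EBI only if patients are not worse off. Lower service use is not in itself a benefit, and the rule would accept lower cost with worse health.
2. **No uncertainty.** Nothing in the rule asks how precisely the cost difference is estimated. Costs driven by inpatient stays are usually very variable, so a difference in the right direction may be chance.
3. **An undefined second route.** Alcohol-related costs may carry the claim if the remaining costs are equal, but the article does not say how equality is judged.
4. **Adjustment that may depend on the data.** If the verdict turns on a sign, a decision to adjust made after seeing imbalance can change it.

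At stake is the economic conclusion, which the article's Discussion says will inform service design and planning. Followed literally, the rule could also leave objective 5 unanswered whenever EBI looks cheaper.

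**Working it through.** **Plan's own figure.** The article gives no error rate for the rule, and no mean or SD of NHS cost, so there is nothing to reproduce. The check is what the rule does as written.

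**Step 1. The rule against the possible results.**

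| Cost, EBI vs control | Health, EBI vs control | What the rule says | What cost and effect together support |
|---|---|---|---|
| Lower | Better or same | Case made | Supports EBI, subject to uncertainty |
| Lower | Worse | Case made | A trade-off; not settled by cost |
| Higher | Any | Cost-effectiveness study needed | Needs cost and effect together |

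The second row is the error of substance. It needs no numerical assumption.

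**Step 2. Equal cost distributions.** Allocation is 1:1 (Trial randomization procedure). Let D = mean cost (EBI) − mean cost (control). With identical distributions the arms are exchangeable, so P(D < 0) = P(D > 0) = 0.50, ties aside, at any sample size. Simulation (40,000 runs per scenario; log-normal costs; CV 1, 2, 3; n = 51, 65, 103, 130 per arm, the evaluable and recruited numbers in Sample Size calculation) gave 0.498 to 0.505 in all 12 scenarios.

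**Step 3. Precision of the cost difference.** As a fraction of mean cost, SE(D) = CV × √(2/n).

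- Smallest: 1 × √(2/130) = 12.4%.
- Middle: 2 × √(2/103) = 27.9%, so a 95% interval of about ±1.96 × 27.9% = ±55% of mean cost.
- Largest: 3 × √(2/51) = 59.4%.

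The CVs are assumed.

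**Step 4. EBI truly dearer (assumed sizes).**

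- EBI 10% dearer: the rule is met with probability 0.22 (n = 130, CV 1) to 0.42 (n = 51, CV 3).
- EBI 20% dearer: 0.07 to 0.35 across the same range.
- In pounds, with an assumed excess of £150 and n = 103 per arm, P = Φ(−150 / (SD × √(2/103))):

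| Assumed SD | SE(D) | 150/SE | P(rule met) |
|---|---|---|---|
| £2000 | £279 | 0.538 | 0.295 |
| £3000 | £418 | 0.359 | 0.360 |
| £5000 | £697 | 0.215 | 0.415 |

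**Step 5. The alcohol-only route.** Suppose equal means not significantly different at 5% (assumed), with n = 65 per arm, CV 2 for each cost component and independent components. Counting either route as success, P(rule met) when all true costs are equal is 0.56, 0.62 and 0.67 for an alcohol share of cost of 70%, 50% and 30%.

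**Step 6. Data available for a better analysis.** Secondary outcome measures gives six-month pre-period data for ED attendances, hospital days and admissions. The Economic part of Data collection/management process states no pre-period for GP or ambulance data. EQ-5D is named at the assessment before randomisation; its follow-up collection rests on the general statement that data are collected at baseline and each follow-up, and on quality of life being listed as an outcome in the Abstract.

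**The case against.** The strongest reply has five parts.

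- **The article does not say that observed means are compared.** It says only that costs are less, and an analysis plan could supply intervals. The wording is indeed an inference. But with a simple comparison and no inferential criterion, direction alone is the natural reading, and adding an interval would not supply the missing health condition.
- **Cost-effectiveness is not abandoned.** A reader might infer that the trial will skip it, or ignore health, whenever EBI is cheaper. The documents do not support that: the rule makes a cost-effectiveness study unnecessary in that case but does not forbid it, EQ-5D is named for the economic analysis, and two other sections promise cost-effectiveness. What stands is a conflict between sections.
- **The 50% follows from symmetry and is not clearly an error rate.** This stands. Any sign comparison gives one half under identical distributions. Equal true total cost here already includes delivering EBI, so choosing EBI in that case is not wrong if health is no worse.
- **The other percentages rest on assumed costs.** This also stands. A reader might infer that the sign will be close to chance in this trial. That is true only if the real difference is small against the real SD, and the article gives neither.
- **The smaller complaints are read too literally.** Equal probably means no material difference, total costs are put first, classification of alcohol-related use is blinded, and the adjustment wording is tentative. These soften the third and fourth weaknesses but do not define equality or settle the adjustment.

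**Conclusion.** The point holds in a limited form. The article fixes a rule under which lower cost alone makes the economic case. It has no condition that health is not worse, no allowance for uncertainty, and an alternative route that depends on an undefined equality. It conflicts with objective 5 and with Analysis of Health Economic measures.

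The missing health condition and the conflict between sections rest on the text alone. The size of the uncertainty problem does not: 0.50 is exact for identical cost distributions on the sign reading and serves as a benchmark only. The 0.22 to 0.42 (EBI 10% dearer), 0.30 to 0.42 (£150 dearer) and 0.56 to 0.67 (either route) depend on the assumptions shown. None of them forecasts how often this trial would draw a wrong conclusion.

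The matter is worth correcting, but it concerns a secondary, economic component.

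**What to change.** Reconcile Economic Evaluation with objective 5 and Analysis of Health Economic measures by removing the sign-only rule.

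1. Whatever the direction of the cost difference, report incremental NHS cost over six months with a 95% confidence interval (for example by bootstrap), incremental EQ-5D outcome or QALYs, and their joint uncertainty. How the joint uncertainty is displayed is a matter of preference.
2. Claim an economic case only from cost and effect together.
3. Fix the adjustment in advance: baseline EQ-5D, baseline SADQ and the pre-randomisation hospital use already planned (ED attendances, admissions, bed days). Do not make it depend on observed imbalance.
4. Keep alcohol-related costs as a labelled secondary breakdown with no decision attached.
5. Confirm that EQ-5D is collected at 12 weeks and 6 months.

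**Cost.** Revised wording and some extra analysis. The main burden is missing follow-up EQ-5D: the plan allows for 50% dropout, so up to about half the patients could need imputation or another explicit method. The adjustment above uses hospital data already planned. Adjusting for full prior service cost, including GP and ambulance use, could not be assumed free of new collection, because no pre-period is stated for those data.
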